#### Statistical power

We ran 5,000 computer simulations of our study design under a wide range of total sample sizes. In brief, a different multivariate distribution was defined for each of the following five diagnostic categories: (1) PD(with or without agoraphobia), (2) SAD, (3) GAD, (4) OCD, and (5) PTSD. Data were simulated to match the disorder-specific response rates (PD = 0.53, SAD = 0.45, GAD = 0.47, OCD = 0.43, PTSD = 0.59) reported in a meta-analysis of 87 studies [135]. The specified *N* for a given simulation was divided equally across the 2 sites and 5 disorder groupings within sites, and random samples of size *N*/10 were drawn for each disorder group for each site, one of which was arbitrarily labeled “train” and the other “test”. Just as we specified in our analytic plan, elastic-net logistic regression models were fit to the train site, and the optimal penalty mix (parameter alpha) and magnitude (parameter lambda) were selected using the average of 10 repeats of a tenfold cross-validation procedure. We then used this model to predict the response at the test site. These predictions (which are individual probabilities of response) and the actual response values were then used to generate ROC curves for the different models to be compared. The control model, which includes only “traditional” self-report measures, was assumed to have a true AUC of 0.63, and the experimental model, which adds CO_2_ and hyperventilation reactivity measures, was simulated to have a true AUC of 0.73. These values and their differences correspond to our minimal effect size of interest.

Then, for each of the simulated data sets, area under the ROC curve (AUC) was compared using DeLong’s test for two correlated ROC curves, as implemented by the `roc.test` function in the “pROC” package in R, with the directional hypothesis that the experimental model has a greater AUC than the control model. At a total sample size of 600 (300 train site/300 test site), 92.2% of simulations found a significant (*p* < 0.05) difference in model performance. Applying the same approach to the comparison of models with only CO_2_ reactivity (no hyperventilation measures) vs. models with only hyperventilation reactivity (no CO_2_ measures), 82.7% of simulations found a significant (*p* < 0.05) superiority of CO_2_ over hyperventilation. The likely reason for this ~ 10% drop in power is that we modeled CO_2_ and hyperventilation reactivity measures as likely to be correlated (*r* = 0.03—0.25) such that hyperventilation would have a smaller, spurious relationship with treatment outcome by proxy. While this makes the mechanistic specificity of CO_2_ reactivity more difficult to detect than if we had assumed independence between CO_2_ and hyperventilation reactivity, these simulations show that we are reasonably well powered to detect the mechanistically specific predictive value of CO_2_ even under this noisy condition. Power curves for these model comparisons at all simulated sample sizes are shown in Fig. 1.

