#### Model development and validation strategy

We will maintain the data collected at each site (UT and BU) as independent data sets. Two sets of models will be developed, one trained to each site’s data, which will then be used to predict the other site’s data. All statistical tests of model predictions will be performed using data from a completely independent sample. This ensures that findings are not merely “statistically significant” in the sense of being improbable under a null hypothesis, but also demonstrates real-world predictive utility by directly showing that predictions based on one clinical sample are likely to generalize to other clinical samples of the same population. We refer to the site used to fit models as the “train site” and the site used to validate models as the “test site”.

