Two strengths of this validation strategy should be emphasized. First, the significance of the biomarkers will be determined by their ability to outperform self-report measures, not just that their coefficients are significantly different from zero. The former speaks to their real-world utility; the latter does not. Second, the biomarkers are being compared on their ability to predict new data, not just their ability to fit the same data. This design/analytic feature helps ensure that we do not propagate failure-to-replicate issues. If we do not replicate a simplified model across sites and our hypotheses are not supported by the data (and there is not support for an alternative model with adequate sensitivity and specificity), we will recommend to the field that reactivity to CO_2_ and/or VH challenge (and the confounder variables we assessed) should not be used for determining patients’ suitability for EBT. Our use of a replicated assessment and a large sample helps instill confidence in these recommendations.

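### The stated power (92.2% and 82.7%) is for one train-to-test direction, but the plan tests each hypothesis in both directions and does not say how the two results combine

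*Protocol article*

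**What the plan says.** All references are to the protocol article.

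- **Statistical power, design simulated.** The total sample was split equally over two sites, "one of which was arbitrarily labeled" the training site and the other the test site. The elastic-net models were fitted at the first and used to predict the second. The section presents this as a simulation of the study design that follows the analytic plan.
- **Statistical power, test and result.** The areas under the ROC curve (AUC) were compared by DeLong's test, "with the directional hypothesis that the experimental model has a greater AUC than the control model". For the first hypothesis, the section reports: "At a total sample size of 600 (300 train site/300 test site), 92.2% of simulations found a significant" difference at p<0.05. For the second, "82.7% of simulations found a significant (*p* < 0.05) superiority of CO_2_ over hyperventilation".
- **Model development and validation strategy, planned analysis.** "Two sets of models will be developed, one trained to each site", and each set is then used to predict the other site. Significant differences between curves are to be evaluated by DeLong's test, with no side named here. The CO2 against hyperventilation comparison follows if the first comparison shows value.
- **Replication language.** The section on the stage model approach describes a replication sample included to ensure consistent prediction. The validation strategy section gives the condition for advising the field against the measures, which begins "If we do not replicate a simplified model across sites and our hypotheses are not supported by the data" and adds a third element: no support for an adequate alternative model.

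**The concern.** The simulated trial makes one comparison per hypothesis and the planned trial makes two. A power figure belongs to a decision rule, and the article gives no rule for turning two directional p-values into one conclusion. The stated figures therefore describe the chance that one chosen direction is significant, which is not the conclusion the replication language points to.

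Two things are at stake. If success means significance in both directions, the mechanistic-specificity hypothesis has less power than stated. If success means significance in either direction, the false-positive rate exceeds the stated 5%. With no rule fixed, the choice could also be made after seeing that the two sites disagree, and the two choices would then lead to opposite conclusions. The result is meant to feed a go/no-go recommendation on starting exposure-based therapy.

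**Working it through.** **Inputs from the article.** Per-direction power is 92.2% (hypothesis 1) and 82.7% (hypothesis 2), one-sided p<0.05, with 300 training and 300 test participants. The control model "was assumed to have a true AUC of 0.63" and the experimental model an AUC of 0.73. Response rates are 0.53, 0.45, 0.47, 0.43 and 0.59 in equal groups.

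**Input not in the article.** The correlation r between the two directional test statistics is not given, so a range is shown.

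**1. Do the stated figures fit a single one-sided direction?**
The mean response rate is (0.53 + 0.45 + 0.47 + 0.43 + 0.59)/5 = 0.494, so a test site of 300 has about 148 responders and 152 non-responders. Hanley–McNeil standard errors are 0.0320 at AUC 0.63 and 0.0290 at AUC 0.73. With correlation c between the two AUC estimates,

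SE(difference) = √(0.0320² + 0.0290² − 2c × 0.0320 × 0.0290), and power = Φ(0.10/SE − 1.645).

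| c | SE | one-sided power |
|---|---|---|
| 0.40 | 0.0335 | 91% |
| 0.43 | 0.0327 | 92% |
| 0.50 | 0.0306 | 95% |

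The figure of 92.2% is consistent with one one-sided test at c of about 0.43. It cannot be reproduced exactly, because the simulated predictor distributions are not given. Nothing suggests that it is wrong for one direction.

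**2. Power if both directions must be significant.**
With per-direction power p, independence gives p²:
- Hypothesis 1: 0.922² = 85.0%.
- Hypothesis 2: 0.827² = 68.4%.

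For any dependence, joint power lies between 2p − 1 and p:
- Hypothesis 1: 84.4% to 92.2%.
- Hypothesis 2: 65.4% to 82.7%.

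With bivariate normal test statistics:

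| r | hypothesis 1 | hypothesis 2 |
|---|---|---|
| 0 | 85.0% | 68.4% |
| 0.1 | 85.2% | 69.1% |
| 0.3 | 85.9% | 70.6% |
| 0.5 | 86.7% | 72.5% |
| 0.7 | 87.8% | 74.8% |
| 0.96 | 90.6% | 79.8% |
| 0.97 | 90.8% | 80.2% |

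Hypothesis 2 reaches 80% only when r exceeds about 0.96.

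As a guide to r, a check simulation used 3,000 runs, two sites of 300, independent control predictors and ridge logistic regression in place of the elastic net. It gave r of about 0.15 under the alternative. Joint power for hypothesis 1 was 89.9%, against 89.6% for the product of the per-direction powers in that simulation. Its predictors are assumed, so it supports the lower part of the range but does not settle the value.

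**3. Error if either direction suffices.**
Assume each direction has exactly 5% one-sided error.
- Independence: 1 − 0.95² = 9.75%.
- r = 0.3: 9.3%.
- r = 0.7: 8.0%.

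Power under this rule, with independence, would be 1 − 0.078² = 99.4% and 1 − 0.173² = 97.0%.

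**4. How often would the sites disagree on hypothesis 2?**
The probability that exactly one direction is significant is 2(p − joint power).
- r = 0: 2(0.827 − 0.684) = 29%.
- r = 0.3: 2(0.827 − 0.706) = 24%.

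At the effect the plan assumes, the missing rule would decide the conclusion in about a quarter of trials.

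**The case against.** The strongest reply is that the article never requires significance in both directions. The sentence on failure to replicate concerns a simplified model, joins that failure with two other conditions, and governs when to recommend against use rather than when a hypothesis is supported. The sample-size section speaks of 300 participants to develop the model and 300 to validate it, which is the one-direction design that was simulated. On that view 92.2% and 82.7% are valid per-direction powers, and an exact combination rule may stand in a fuller document that is not shown.

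Much of this stands. A reader might infer that the plan already demands both directions and that its power is therefore simply 85% and 70%. The text does not support that: those values depend on a rule the article does not state and on a correlation it does not give. Nor are the stated figures shown to be miscalculated.

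A reader might also note that the second test depends on the first and put a figure, such as about 60%, on completing the whole sequence in both directions. The ordering is real, so 82.7% is not the chance of reaching the specificity claim through the sequence. But reporting power per hypothesis is ordinary practice, and a sequence figure depends on predictor distributions that the article does not give.

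The reply does not remove the mismatch. The article itself states the power, describes the simulation as following the analytic plan, and describes a plan with twice as many tests. Wherever the rule is written, the published pair of 5% error and 92.2%/82.7% power fits neither the both-directions nor the either-direction rule.

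**Conclusion.** The point holds in this form: the stated power covers one direction, the plan tests two, and the article does not fix how they combine.

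- **Both required:** about 85% for hypothesis 1 (bounds 84.4–92.2%). For hypothesis 2, about 68–71% at correlations of 0 to 0.3 and about 75% at 0.7 (bounds 65.4–82.7%). Hypothesis 2 stays below 80% unless the two directions are almost perfectly correlated.
- **Either suffices:** one-sided error of about 8–10% for correlations from 0.7 down to 0.

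These results take the article's per-direction powers as correct, the same in each direction and one-sided at 5%. The intermediate values also assume bivariate normal test statistics; the bounds do not. The finding does not show the sample size or the DeLong comparison to be invalid. It shows that the stated operating characteristics do not belong to the two-direction analysis described.

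**What to change.** Before any test-site outcomes are analysed:

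1. State the decision rule for each hypothesis and the side of the test. One-sided p<0.05 in both directions best fits the replication language, and it keeps the error at or below 5% whatever the correlation. A pooled or averaged rule would also be defensible if stated in advance with its own error and power.
2. Re-run the existing simulation code with both directions in each simulated trial, under that rule. Replace 92.2% and 82.7% with the result, or label them as per-direction power.
3. If power for the whole sequence of two hypotheses is wanted, take it from that same re-run.
4. Describe the two directions as a swapped pair using the same two data sets, not as two independent replications.

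The cost is plan wording and computing time. Under a both-directions rule the stated power becomes less favourable, most visibly for the specificity hypothesis. No extra patients are needed.

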**Methods:**

We will assess CO_2_ reactivity in 600 adults meeting criteria for one or more fear- or anxiety-related disorders prior to providing open exposure-based therapy. By incorporating CO_2_ reactivity into a multivariate model predicting treatment non-response that also includes reactivity to hyperventilation as well as a number of related predictor variables, we will establish the mechanistic specificity and the additive predictive utility of the potential CO_2_ reactivity biomarker. By developing models independently within two study sites (University of Texas at Austin and Boston University) and predicting the other site’s data, we will validate that the results are likely to generalize to future clinical samples.

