### Sample size and data analytic approach

Simulation work has shown that large sample sizes are required to develop accurate predictive models of treatment response [102, 103]. Our own statistical simulation shows that given the two-site, split-half validation design, we require 300 participants per site—at least 300 to develop the model and another 300 to adequately validate it in this Stage 1 model. The reality is that underpowered studies likely detect only the largest effects, and multivariate models based on them yield unstable predictions that overfit the sample data and perform poorly out-of-sample [104, 105]. As pointed out by Kessler and colleagues, “The inevitable conclusion is that samples much larger than those in existing mental disorder randomized clinical trials are required to develop useful personalized treatment recommendations” [106]. The overarching message of the statistical learning literature and our own simulations used to develop this proposal is “go big or go home”.

Our primary objective is to build a model predicting EBT non-response using a multivariate combination of candidate predictors. One set of predictors constitutes what we consider our “control” model; these include “traditional” prognostic factors and psychological variables (see Table 1). The addition of a second set of predictors, corresponding to our proposed measures of reactivity to CO_2_ and VH, constitutes our “experimental” model. We have two key hypotheses that we aim to test: (1) the experimental model will outperform the control model when predicting never-before-seen data, establishing the additive predictive value of assessing reactivity measures prior to initiating treatment; and (2) when predicting never-before-seen data, a model that excludes VH reactivity measures will outperform a model that excludes CO_2_ reactivity measures, establishing that the additive predictive value is specific to CO_2_ reactivity.

**Table 1 Tab1:** Schedule of assessments

Measurement Domain	Screen	Biomarker Visit	Treatment (Weeks 1–12)	Follow-up (Weeks 13, 24)

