## Methods/design

### Design

We aim to recruit a transdiagnostic sample (*N* = 300 at each of two collaborating sites [The University of Texas at Austin (UT) and Boston University (BU)]) presenting with one or more DSM-5 anxiety disorders, OCD, or PTSD. Eligible participants will complete 20% CO_2_ and VH challenges, as well as a comprehensive set of clinician-rated and patient-rated measures prior to starting open, transdiagnostic, EBT. Assessment of non-response will occur weekly during treatment, at 1-week posttreatment (i.e., primary endpoint), and at 3-month follow-up. This study has been registered with ClinicalTrials.gov (NCT05467683; 20/07/2022). The UT Institutional Review Board has approved the study protocol for both participating sites (STUDY00001631).

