### Participants

The transdiagnostic sample will consist of 600 participants. Inclusion criteria include: (1) a primary DSM-5 diagnosis of PD (with or without agoraphobia), SAD, GAD, OCD or PTSD; (2) a score of 8 or greater on the Overall Anxiety Severity and Impairment Scale (OASIS) [107]; (3) ages 18–70; (4) willingness and ability to provide informed consent and comply with the requirements of the study protocol; and (5) proficiency in English (because many assessment instruments have only been validated in English). Exclusion criteria include: (1) a lifetime history of bipolar or psychotic disorders; substance use disorders (other than nicotine) or eating disorder in the past 6 months; serious cognitive impairment; (2) active suicidal ideation with at least some intent to act with or without a specific plan (i.e., a rating of 4 for suicidal ideation on the Columbia-Suicide Severity Rating Scale; CSSRS) [108] or suicidal behaviors (actual attempt, interrupted attempt, aborted or self-interrupted attempt, or preparatory acts or behavior) within the past 6 months; (3) medical conditions contraindicating CO_2_ inhalation or VH (e.g., cardiac arrhythmia, cardiac failure, asthma, lung fibrosis, stage 2 high blood pressure, epilepsy, or stroke); (4) pregnancy or lactation; (5) ongoing psychotherapy directed toward the primary disorder; or (6) pharmacological treatment started within 8 weeks prior to the screen (participants “stable” on their medication regimen will be included and their medication status will be included as a variable in the model).

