#### Retention

We include an incentive-based approach that includes; (1) obtaining multiple methods for contacting participants; (2) offering flexibility in scheduling appointments; (3) personalized connections around scheduling; (4) providing reminders of appointments; and (5) weekly monitoring of recruitment and retention and quality control across sites. Also, assessment adherence and study completion will be aided by study compensation. Compensation is based on one biomarker assessment session, one baseline session, 12 weekly assessment sessions, 1 posttreatment and 1 follow-up assessment at the following levels: $70 for the biomarker assessment session, $30 for the baseline assessment, $10 for each weekly assessment ($120), and $30 for posttreatment and follow-up ($60), plus a reward of $20 for completing all assessments, for a total of $300 per participant.

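### The stated power assumes 300 known outcomes per site, which is also the number recruited before therapy; with no attrition allowance, the CO2-versus-VH test drops below 80% power beyond about 7–8% missing outcomes

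*Protocol article*

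**What the plan says.** **Number required.** Sample size and data analytic approach says that, for the two-site split, "we require 300 participants per site—at least 300 to develop the model and another 300 to adequately validate it".

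**Number behind the power.** Statistical power states: "At a total sample size of 600 (300 train site/300 test site), 92.2% of simulations found a significant" difference between the control and experimental models. At the same size it gives 82.7% for CO2 over VH. The test is a directional DeLong comparison at 0.05. Patients are drawn as N/10 per disorder per site, and predictions are compared with their actual responses. No attrition step is described.

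**Number recruited.** Design sets the target at "300 at each of two collaborating sites", and Participants says "The transdiagnostic sample will consist of 600 participants". The Abstract (Methods) places the count before treatment: CO2 reactivity will be assessed "in 600 adults meeting criteria for one or more fear- or anxiety-related disorders prior to providing open exposure-based therapy".

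**Time to outcome.** Therapy is 12 sessions over 12 weeks. The primary endpoint is one week after treatment (week 13). CGI and OASIS are also rated weekly during treatment.

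**Loss.** The Retention section lists measures such as "weekly monitoring of recruitment and retention", payment per assessment and a completion reward. It gives no expected rate of loss and no inflation of the sample.

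**The concern.** The number called necessary, the number simulated with complete outcomes and the number entering therapy are all 300 per site. The stated power therefore holds only if every patient assessed at the biomarker visit yields a usable week-13 outcome.

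The comparison with the thinner margin is CO2 versus VH. It carries the second key hypothesis, that any predictive gain is specific to CO2 reactivity, and the article describes its power for that test as reasonable. Under Model development and validation strategy, the investigators also commit to a negative recommendation to the field if the hypotheses are not supported and no adequate alternative model emerges. They cite the large sample as a reason for confidence in it. If the power is lower than stated, a null result on specificity is weaker evidence than the article implies.

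**Working it through.** **Inputs from the article:** 300 train and 300 test; power 92.2% and 82.7%; one-sided 5% (z = 1.645); AUC 0.63 and 0.73; response rates 0.53, 0.45, 0.47, 0.43 and 0.59 in equal groups (mean 2.47/5 = 0.494). **Assumed:** the loss rates, and analysis of complete cases.

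**Step 1. Can the stated figures be reproduced?**
- *Experimental versus control.* Hanley–McNeil standard errors at n = 300 with 49.4% responders are 0.0320 (AUC 0.63) and 0.0290 (AUC 0.73). Power = Φ(0.10/SE_diff − 1.645), where SE_diff² = 0.0320² + 0.0290² − 2r(0.0320)(0.0290). The correlation r between the two AUC estimates is not given. Power is 86.8% at r = 0.3, 91.0% at r = 0.4 and 94.7% at r = 0.5. The stated 92.2% needs r of about 0.43. It is plausible but cannot be strictly reproduced.
- *CO2 versus VH.* The AUCs for these two models are not stated, so 82.7% cannot be reproduced.

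Both stated powers are therefore taken as correct.

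**Step 2. Scale for missing outcomes.** The noncentrality is λ = 1.645 + Φ⁻¹(stated power):
- Experimental versus control: 1.645 + 1.419 = 3.064
- CO2 versus VH: 1.645 + 0.942 = 2.587

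With a fraction d of outcomes missing, power(d) = Φ(λ√(1 − d) − 1.645).

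| Assumed loss d | With outcome per site | √(1 − d) | Experimental vs control | CO2 vs VH |
|---|---|---|---|---|
| 0% | 300 | 1 | 92.2% | 82.7% |
| 5% | 285 | 0.975 | 91.0% | 81.0% |
| 10% | 270 | 0.949 | 89.6% | 79.1% |
| 15% | 255 | 0.922 | 88.1% | 77.0% |
| 20% | 240 | 0.894 | 86.3% | 74.8% |

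Worked case, CO2 versus VH at 10%: 2.587 × 0.949 − 1.645 = 0.810, and Φ(0.810) = 0.791.

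**Step 3. Loss at which power reaches 80%.** d = 1 − ((1.645 + 0.842)/λ)².
- CO2 versus VH: 1 − (2.487/2.587)² = about 7.6%
- Experimental versus control: 1 − (2.487/3.064)² = about 34%

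**Step 4. Check of the scaling.** A simplified train/test simulation was run for experimental versus control, with ridge logistic regression in place of the tuned elastic net and three assumed predictor sets. One-sided power was 94.2, 95.9 and 94.1% at 300/300, and 89.7, 90.7 and 89.8% at 240/240. Applying the Step 2 formula to those starting values at d = 0.20 predicts 89.1, 91.7 and 89.0%, so the scaling is about right. The absolute levels differ from the article's because the predictor structure is assumed.

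**Limit.** The formula reflects only the smaller test set. Fitting on fewer training patients would lower both powers somewhat more. In the simplified simulation that extra effect was slight: the mean AUC gap changed by about 0.002 or less between 300 and 240 per site.

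**The case against.** The strongest reply is that leaving therapy is not the same as lacking an outcome. The independent evaluator rates CGI by telehealth, CGI and OASIS are collected every week, and patients are paid for each assessment, including posttreatment. Someone who stops therapy may still have a week-13 rating, or weekly ratings from which one can be imputed. This stands. A reader might infer that any dropout puts the stated power out of reach, and the documents do not support that. At 5% missing outcomes both powers fall by less than 2 points, and the first comparison keeps 80% until about a third of outcomes are lost.

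A reader might also infer that the plan leaves out patients without week-13 data. It does not say so. The definition of non-response is silent on missing outcomes, and the rule may sit in an analysis plan that is not shown, so its absence is not a fault here. The complete-case figures show the size of the exposure, not what the plan will do.

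Two further replies carry some weight. The article sets no 80% threshold, and it says that power at other sample sizes is plotted in its figure. Neither changes the point: the text presents the power at 300 per site as what the design delivers, and that is the number before any loss. The retention measures are routine and do not show that the sponsor expects a particular rate.

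**Conclusion.** The point holds in limited form. Neither 92.2% nor 82.7% is shown to be miscalculated; both are tied to complete outcomes in everyone recruited, with no allowance for attrition. Experimental versus control has ample room. CO2 versus VH does not: it falls below 80% once more than about 7–8% of outcomes are missing, and to about 75% at 20%.

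These sizes rest on assumed loss rates, complete cases, a one-sided 5% test, the stated powers being right, and scaling of the test set alone. Imputation from informative weekly ratings would make the loss smaller; the smaller training set would make it somewhat larger.

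**What to change.** Restate both powers at the number of patients per site expected to have a week-13 outcome, and state the loss rate used. The sponsor has already simulated a range of total sample sizes, so this needs only a reading from existing results. Qualify the description of power for the CO2-specificity test to match.

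To limit the loss, multiply impute week-13 non-response from the weekly CGI and OASIS ratings, with missing counted as non-response in a sensitivity analysis. If the unseen analysis plan already specifies this, a cross-reference is enough.

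The cost is a slightly less favourable stated power and modest extra analysis. No patients or visits are added.

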Hypothesis testing will be based on a series of model comparisons. All models will be fit to the train site and used to predict the probability of treatment response at the test site. These probabilities will be used to generate an ROC curve for each model’s ability to discriminate treatment responders from non-responders. Significant differences between curves will be evaluated using DeLong’s test for two correlated ROC curves as implemented by the R package “pROC”. The following model comparisons will be performed:All candidate predictors vs. excluding CO_2_/VH reactivity measures. This comparison addresses the question: do the novel measures of CO_2_/VH reactivity add predictive value beyond traditional—and easier to collect—measures like diagnosis or symptom severity? We hypothesize that the addition of the reactivity measures will significantly improve model performance. If CO_2_ reactivity is completely confounded with these competing predictors, then adding it to the model will not result in any predictive gains; CO_2_ reactivity can only improve model predictions if it provides unique information that is not captured by “confounders”.CO_2_ vs. VH reactivity. Finally, if the above model demonstrates the value of collecting CO_2_ reactivity measures, we will next assess does CO_2_ reactivity specifically predict treatment non-response (by revealing something about the underlying biology), or is it merely heightened sensitivity to the physiological sensations that are common to both CO_2_ inhalation and hyperventilation? Qualitatively, if VH reactivity has no predictive utility, then the statistical learning algorithm will have penalized these measures out of the model entirely by this point. However, the hypothesis of mechanistic specificity will be more formally tested by comparing a model that includes just CO_2_ reactivity measures to one that includes just VH reactivity measures. Note that the ability to perform a head-to-head comparison like this is one of the advantages of comparing ROC curves in an independent test set; the models do not need to be nested as they would when performing likelihood ratio tests on model fits.

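### The 82.7% power for CO2 versus VH is the marginal power of that test; if the test is run only after comparison 1 succeeds, 82.7% is an upper bound

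*Protocol article*

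**What the plan says.** Three sections of the protocol article bear on this.

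- **Sample size and data analytic approach.** "We have two key hypotheses that we aim to test": first, that the experimental model outperforms the control model; second, that the added value is specific to CO2. Neither is made conditional on the other.
- **Model development and validation strategy.** Two comparisons are listed, each judged by DeLong's test at the test site. For comparison 1 (all predictors versus all except the reactivity measures) the expectation is stated as "We hypothesize that the addition of the reactivity measures will significantly improve model performance". Comparison 2 (CO2 versus VH) is introduced with "if the above model demonstrates the value of collecting CO_2_ reactivity measures, we will next assess".
- **Statistical power.** The procedure is that "for each of the simulated data sets, area under the ROC curve (AUC) was compared using DeLong’s test". At 300 train and 300 test participants, "92.2% of simulations found a significant (*p* < 0.05) difference in model performance". The second figure is obtained by "Applying the same approach to the comparison of models with only CO_2_ reactivity (no hyperventilation measures") against models with VH only, and "82.7% of simulations found a significant" advantage for CO2. The section attributes the drop from the first figure to the second to correlation between the CO2 and VH measures, and concludes that power for mechanistic specificity is adequate. It does not mention the conditional clause and gives no joint power.

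**The concern.** If comparison 2 is carried out only after comparison 1 has succeeded, a simulated trial that fails comparison 1 cannot support specificity, whatever its CO2-versus-VH test would have shown. The count behind 82.7% does not appear to remove such trials. It would then be the power of a test that is always run, whereas the analysis section describes one that is run conditionally.

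Two things are at stake. First, the statement that the study has adequate power for specificity rests on a figure that may not belong to the procedure described. Second, if comparison 1 narrowly fails, one section implies that hypothesis 2 is still tested and another implies that it is not. Under the design assumptions this situation arises in 100% − 92.2% = 7.8% of trials. The choice should not be left until test-site results are known.

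**Working it through.** **Inputs, all from Statistical power:** power of comparison 1, P1 = 0.922; power of comparison 2, P2 = 0.827; directional test at p < 0.05; 300 test participants; true AUCs 0.63 and 0.73 for comparison 1; five disorder response rates averaging (0.53 + 0.45 + 0.47 + 0.43 + 0.59)/5 = 0.494, hence about 148 responders and 152 non-responders. All figures below refer to one train-test direction.

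**Step 1: are the stated powers plausible?**

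For comparison 1, the Hanley-McNeil variances give a standard error of the AUC difference of 0.0432 if the two AUCs are uncorrelated and 0.0335 if they correlate at 0.4. In the second case power = Φ(0.10/0.0335 − 1.645) = Φ(1.34) ≈ 0.91. At a correlation of 0.5 it is about 0.95. So 92.2% is plausible for a correlation between 0.4 and 0.5, which the article does not state.

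For comparison 2, the article gives neither the AUCs nor the predictor distributions. The 82.7% cannot be reproduced and is taken as stated.

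**Step 2: what the two figures fix without further assumption.**

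- Lower bound: P1 + P2 − 1 = 0.922 + 0.827 − 1 = 0.749.
- Upper bound: min(P1, P2) = 0.827.
- Independence: 0.922 × 0.827 = 0.762.

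The loss relative to 82.7% is therefore between 0 and 7.8 points.

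**Step 3: dependence on the correlation of the two test statistics.** With a bivariate normal model, the joint power is P(Z1 < 1.419, Z2 < 0.942) at correlation r. Dividing by 0.922 gives the power of comparison 2 among trials that pass comparison 1.

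| r (assumed) | Both significant | Comparison 2 given comparison 1 |
|---|---|---|
| 0 | 76.2% | 82.7% |
| 0.2 | 77.1% | 83.6% |
| 0.3 | 77.6% | 84.2% |
| 0.5 | 78.8% | 85.4% |
| 0.6 | 79.5% | 86.2% |
| 0.7 | 80.2% | 87.0% |
| 0.9 | 82.1% | 89.0% |

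**Step 4: which r is reasonable?** A train/test simulation used ridge-penalised logistic models (not the elastic net) and DeLong's test, with 1,200 replicates per setting. The VH effect was tuned to bring comparison 2 near its stated power. With 8 control, 4 CO2 and 4 VH predictors:

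- control predictors kept in both models: powers 92.9% and 83.0%, both significant 79.7%, r = 0.52;
- reactivity measures only: powers 92.7% and 84.0%, both significant 79.1%, r = 0.19.

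With one predictor of each kind, the settings nearest the stated power had r = 0.65 and 0.30. These runs support r of roughly 0.2 to 0.7, hence 77% to 80% at the stated powers. The inputs for comparison 2 had to be assumed, so this range is illustrative.

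**The case against.** The strongest reply is that nothing printed is wrong. The article describes 82.7% as the share of simulations in which CO2 beat VH, reporting power hypothesis by hypothesis is normal, and the two hypotheses are listed separately. That stands: 82.7% is a correct kind of figure for that test taken alone, and a reader who infers an arithmetic error goes further than the text allows.

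The conditional clause can also be read as the scientific order of two questions. It names no p-value and does not say that comparison 2 is skipped after a non-significant comparison 1. The list is itself introduced as comparisons that will be done. This stands in part. Reading the clause as a significance condition is an inference, but it is the natural one, since significance is the only criterion the section offers for comparison 1.

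A reader might also infer that true power is 77% to 80% and that the study misses an 80% target. The documents support neither. The narrower range rests on a correlation they do not give, and no 80% target is stated. If the correlation is very high the loss is small: 0.6 points at r = 0.9. Among trials in which comparison 2 is actually reached, its power is at least 82.7% for any non-negative correlation.

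Finally, a condensed article may leave formal testing rules to a fuller document. Here, though, the article itself states the hypotheses, the procedure and the power, and these do not match one another.

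**Conclusion.** The point holds as an inconsistency between three sections, with a modest numerical consequence. The power figure and the hypothesis list describe a CO2-versus-VH test that is always run; the analysis section describes one that follows only a successful comparison 1.

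If the condition applies, 82.7% is the upper bound of the chance of establishing specificity. The stated powers alone fix that chance at 74.9% to 82.7%. The figures of 76.2% and about 77% to 80% require, respectively, independence and an assumed correlation of 0.2 to 0.7 between the test statistics. If the condition does not apply, 82.7% stands as printed. Neither reading calls the sample size into question.

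**What to change.** Choose one of two courses and word all three sections accordingly, before test-site results are seen.

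- **Always test hypothesis 2.** Remove the conditional clause in Model development and validation strategy. The 82.7% then applies unchanged.
- **Keep the condition.** State in Model development and validation strategy what counts as success in comparison 1 (for example, the DeLong test at the stated level), and add the same condition to the hypotheses in Sample size and data analytic approach. In Statistical power, re-count the existing simulations and report the share in which both comparisons are significant as the power for specificity. The 82.7% can remain beside it, labelled as the marginal power of comparison 2.

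The cost is a re-count of simulation output and a few words of text (or a rerun, if the per-trial results were not kept). Under the second course the stated power may become slightly less favourable.
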